Mucositis	Erythema of the mucosa	Patchy pseudomembranes or ulcerations	Confluent pseudomembranes or ulcerations OR mucosal bleeding with minor trauma
Hematuria	Microscopic hematuria	Frank hematuria with normal serum creatinine (within the normal range for age)	Frank hematuria with elevated (outside of the normal range for age) serum creatinine
Nausea	Nausea with decreased oral intake not requiring intravenous rehydration	Nausea with decrease oral intake requiring intravenous rehydration	Inadequate oral fluid and caloric intake with resulting hypotension or weight loss
Vomiting	1–3 episodes in 24 h with no or mild dehydration	4–6 episodes in 24 h or any amount with moderate dehydration requiring intensive intravenous rehydration	> 6 episodes in 24 h or any amount of vomiting resulting in persistent hypotension

*ULN* Upper limit of normal, *SGOT* Serum glutamic-oxaloacetic transaminase

^a^Platelets and hemoglobin are expected to be abnormal in participants with uncomplicated malaria

**Table 3 Tab3:** Toxicity grading scales for pediatric participants

Parameter	Grade 1	Grade 2	Grade 3
White blood cells (10^3^/μL)	2.0–2.39 if normal baseline	1.5–1.99 if normal baseline	< 1.5 if normal baseline
			65% reduction from baseline, if abnormal baseline
	35% reduction from baseline, if abnormal baseline	50% reduction from baseline, if abnormal baseline	
Hematocrit (PCV)	Not applicable as ongoing anemia and need for blood transfusions not unexpected		
Platelets (10^3^/μL)	100–116 if normal baseline	50–99 if normal baseline	< 50 if normal baseline
		50% reduction from baseline if abnormal baseline	65% reduction from baseline, if abnormal baseline
	35% reduction from baseline, if abnormal baseline		
Serum creatinine	35% increase from baseline	50% increase from baseline	65% increase from baseline
Serum SGOT	1.25 to < 2.5 × ULN if normal baseline	2.5 to < 5.0 × ULN if normal baseline	≥ 5.0 × ULN if normal baseline
			65% increase from baseline, if abnormal baseline
		50% increase from baseline, if abnormal baseline	
	35% increase from baseline, if abnormal baseline		
Serum glucose	Not applicable: hypoglycemia during first 72 h of admission with CM is not unexpected and is closely monitored		
Serum lactate	Not applicable: hyperlactatemia during first 72 h of admission with CM is not unexpected and is closely monitored		

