Diarrhea	3 or more loose stools in 24 h, treated with dietary changes	6 or more loose stools in 24 h requiring IV rehydration for clinical stabilization, resolving within 36 h	6 or more loose stools in 24 h requiring IV rehydration for clinical stabilization, not resolving within 36 h
Gastrointestinal bleeding	Coffee ground emesis or positive stool hemoccult or frank bleeding with < 10% decrease in hematocrit/PCV	Coffee ground emesis or positive stool hemoccult or frank bleeding with a ≥ 10% decrease in hematocrit/PCV not requiring transfusion	Coffee ground emesis or positive stool hemoccult or frank bleeding with a ≥ 10% decrease in hematocrit/PCV requiring transfusion
Mucositis	Erythema of the mucosa	Patchy pseudomembranes or ulcerations	Confluent pseudomembranes or ulcerations OR mucosal bleeding with minor trauma
Hematuria	Microscopic hematuria	Frank hematuria with normal serum creatinine (within the normal range for age)	Frank hematuria with abnormally elevated (outside of the normal range for age) serum creatinine
Vomiting	1–3 episodes in 24 h with no or mild dehydration	4–6 episodes in 24 h or any amount of vomiting with moderate dehydration requiring intensive intravenous rehydration	More than 6 episodes in 24 h resulting in persistent hypotension

Laboratory parameters impacted by cerebral malaria are expected to be disordered prior to DON administration

*ULN* Upper limit of normal, *SGOT* Serum glutamic-oxaloacetic transaminase, *PCV* Packed cell volume

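### Pediatric Table 3 grades GI bleeding by a PCV fall and transfusion that need not come from the bleed, and its hematuria and creatinine rows use different creatinine references

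*Protocol article*

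**What the plan says.** All of this is in the Protocol article, section Primary endpoints, Table 3 (pediatric grading).

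- **PCV row.** Hematocrit is not graded: "Not applicable as ongoing anemia and need for blood transfusions not unexpected".
- **GI bleeding row.** Grade 1: "Coffee ground emesis or positive stool hemoccult or frank bleeding with < 10% decrease in hematocrit/PCV". Grade 2: "Coffee ground emesis or positive stool hemoccult or frank bleeding with a ≥ 10% decrease in hematocrit/PCV not requiring transfusion". Grade 3: "Coffee ground emesis or positive stool hemoccult or frank bleeding with a ≥ 10% decrease in hematocrit/PCV requiring transfusion".
- **Hematuria row.** Grade 1 is "Microscopic hematuria". Grade 2 is frank hematuria with creatinine normal for age. Grade 3 is "Frank hematuria with abnormally elevated (outside of the normal range for age) serum creatinine".
- **Creatinine row.** Graded only by rise from baseline: 35%, 50% and 65% for grades 1, 2 and 3.
- **Footnote.** "Laboratory parameters impacted by cerebral malaria are expected to be disordered prior to DON administration". It does not name creatinine.

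Table 1 admits children with a PCV of 18% or more and lists no creatinine limit for them. For adults it does list one.

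**The concern.** A severity grade should rank the event it is attached to. In the pediatric GI bleeding row, the bleeding signs are constant across grades, so the grade is decided by the course of PCV and by transfusion. The same table treats both as part of the disease. A child with an occult-positive stool and malarial anemia can then be recorded with a moderate or severe bleed.

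The hematuria row has a related but smaller fault. Its step from grade 2 to 3 depends on where creatinine stands, not on whether it has changed since dosing.

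At stake is how readable the bleeding severity data are. The Discussion names gastrointestinal bleeding as a potential risk of DON. The section on adverse event reporting has severity recorded with these tables, and the DSMB reviews solicited and unsolicited AEs when it advises on dose escalation.

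**Working it through.** The plan states no figure that depends on these rows, so there is none to reproduce. The check sets the rows side by side and works out the thresholds.

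**1. What separates the GI bleeding grades.** Each grade accepts any of three signs: coffee ground emesis, a positive hemoccult or frank bleeding. The remaining criteria are:

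| Grade | PCV fall | Transfusion |
|---|---|---|
| 1 | < 10% | not mentioned |
| 2 | ≥ 10% | no |
| 3 | ≥ 10% | yes |

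No cell requires the fall or the transfusion to result from the bleed. Take an illustrative child whose PCV goes from 20% to 17% through malaria and who is transfused. The relative fall is (20 − 17)/20 = 15%. With no bleeding sign, Table 3 records nothing for PCV. With a positive hemoccult, it records a grade 3 GI bleed. A child with frank bleeding whose PCV is maintained is grade 1.

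**2. What 10% means.** PCV is itself a percentage and the row gives no reference. For baseline PCV *b*, a relative fall leads to 0.9 × *b* and an absolute fall to *b* − 10. Only the 18% is a document figure (Table 1); the other baselines are illustrative.

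| Baseline PCV | Relative 10% fall | Points lost | Absolute 10-point fall |
|---|---|---|---|
| 18% | 16.2% | 1.8 | 8% |
| 20% | 18.0% | 2.0 | 10% |
| 25% | 22.5% | 2.5 | 15% |
| 30% | 27.0% | 3.0 | 20% |

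On the relative reading, 2 to 3 points are enough, so the course of malaria alone can plausibly cross the line. On the absolute reading it rarely would. The size of the problem therefore depends on a reading that the table leaves open.

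**3. Hematuria against creatinine.** Assumed creatinine levels, as multiples of the upper limit of normal (ULN):

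- Unchanged at 1.05 to 1.5 × ULN: the rise is 0%, so there is no creatinine grade, yet frank hematuria is grade 3. Creatinine grade 3 would need 1.05 × 1.65 = 1.73 to 1.5 × 1.65 = 2.475 × ULN.
- Rising from 0.5 to 0.95 × ULN: 0.95/0.5 − 1 = 90%, which is creatinine grade 3, yet frank hematuria stays grade 2.

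The two rows can thus point in opposite directions for the same child.

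**4. Weight of one misgraded child at the interim.** The Sample size section gives 28 DON and 8 placebo children after cohorts 1 to 3; the 28 are 14 per dose. One misgraded child moves the observed proportion by 1/14 = 7.1 percentage points in a dose group and by 1/8 = 12.5 points on placebo.

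**5. What cannot be computed.** The documents give neither the distribution of PCV change nor the frequency of bleeding signs, so no misgrading rate can be derived.

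**The case against.** **Reach.** Grade 2 and 3 AEs enter the adult primary endpoint only. The pediatric primary endpoint and halting rules count SAEs, and under Interim analyses dose choice rests on the primary safety endpoint and exploratory efficacy. No stated rule turns on a GI bleeding grade. This stands and makes the point minor.

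**Attribution and blinding.** Each AE is also assessed for relatedness to study drug and for other causes, and evaluators are blinded. Disease-driven grades should fall on all arms alike, so the result is noise, not bias. That is correct, but attribution of the event to the drug does not correct its severity grade.

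**Convention.** Grading a bleed by its consequence is legitimate, and the diarrhea and vomiting rows do much the same. This stands: there is no case for re-ranking bleeds by appearance. A consequence scale still needs the consequence to belong to the event.

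**The 10%.** Other percentage laboratory changes in Table 3 are stated from baseline, so the relative reading is the natural one. Probably so, but it is also the reading under which malarial anemia most easily sets the grade.

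**Stronger readings that the documents do not support.**

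- A reader might infer that trivial urinary bleeding is also lifted to grade 2 or 3. It is not: microscopic hematuria is grade 1 at any creatinine, and the higher grades both need frank hematuria.
- A reader might infer that the table calls raised creatinine expected. Its own row grades creatinine; only the general footnote leans that way.
- The article expands SAE as severe in some places and as serious in the abbreviation list, so a reader might infer that these grades feed the primary endpoint. Nothing defines an SAE by grade, and the AE reporting section lists severity and seriousness as separate items.

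**Conclusion.** The point holds for pediatric AE severity grading and is minor. As written, the GI bleeding row lets malarial anemia and transfusion turn a trivial sign, such as a positive hemoccult, into grade 2 or 3. The PCV row of the same table sets those quantities aside. This follows from the wording and needs no assumption about rates. How easily it happens depends on the unstated meaning of 10%: at PCV 18%, a fall of 1.8 points or of 10.

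For hematuria the finding is narrower. Frank hematuria, already at least grade 2, can move to grade 3 on admission renal function alone, because that row and the creatinine row use different references. The multiples of ULN used to show this are assumed.

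The consequence is noisier and partly misordered severity data before the DSMB. Neither the primary endpoint nor the halting rules are affected.

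**What to change.** Reconcile the rows of Table 3:

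1. **GI bleeding.** Count a PCV fall or a transfusion toward the grade only when the blinded study clinician judges it due to the bleed.
2. **The 10%.** State that it is a relative fall from the last PCV before the bleed.
3. **Hematuria.** Express the creatinine criterion as change from baseline, as in the creatinine row. The study team should choose and state the cut-off.

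The order of the bleeding signs can stay as it is.

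The cost is two table rows and the matching grading guide for the case report form. Clinicians already assess alternative causes for each AE, so little new data collection is needed. The downside is that the GI bleeding grade will then depend on some clinical judgement, which must be made blind to allocation.

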This clinical trial aims to establish the preliminary safety and efficacy of one such novel therapy, 6-diazo-5-oxo-L-norleucine (DON), a glutamine antagonist. DON has a potent inhibitory effect on a variety of glutamine utilizing pathways including those involved in T cell metabolism. We showed that DON is highly efficacious in treating ECM in mice late in the disease when it has progressed to a point where significant brain swelling and BBB dysfunction have occurred [24]. DON both blocks the progression of ECM and promotes recovery [24, 25]. In a separate study, we used magnetic resonance imaging (MRI) to longitudinally monitor responses to treatment in mice with ECM. We found disease progression mirrored that observed in MRI studies in children with CM, and that, in mice, DON treatment resolved severe brain swelling, which is highly predictive of a fatal outcome [25, 26].

This is not the first clinical trial of DON in humans. DON safety in adults and children with cancer was established in phase I and II clinical trials performed over 40 years ago but did not enter therapeutic use due to a lack of consistent anti-tumor efficacy [17, 27–40]. Most of these studies were multi-dose, covered a wide range of DON treatment regimens, and all were in patients who had failed primary anti-cancer treatment courses. The most commonly reported adverse effects in these studies were nausea and vomiting. However, DON was not evaluated in a single dose, dose-escalation study with concomitant pharmacokinetic (PK) analysis. Therefore, before proceeding to efficacy trials of DON for treatment pediatric CM, we first evaluate DON’s safety in healthy Malawian adults and Malawian adults with uncomplicated malaria before moving to the target population, critically ill children with CM. In the dose-escalation phase I/IIa trial described herein, participants are premedicated with an antiemetic to prophylactically target the most common adverse effects. We will determine the safety profile and PK of a single dose of DON in healthy adult participants and adults with uncomplicated malaria over a dose range of 0.1 mg/kg to 10 mg/kg before assessing safety and efficacy in children with CM.

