#### Pediatric halting rules

The pediatric study pauses enrollment if the number of participants with SAEs in any single MedDRA group exceeds rates expected in children with CM. The expected rates were derived from calculating the cumulative probability of stopping when the true rate of the proportion of participants in a specific MedDRA classification group is a given percent (i.e., 25, 30, 40 or 50%). For example, 9 participants out of the first 17 enrolled must have an SAE within a single MedDRA classification group for the study to pause for review. (This will indicate a single important toxicity that should be considered before further enrollments.) A halt is not triggered, however, if of the first 17 enrolled pediatric participants, 9 experience SAEs in different MedDRA classification groups (e.g., 3 participants die, 3 participants have renal failure, and 3 participants have severe thrombocytopenia). High rates of both adverse outcomes and abnormal laboratory values are expected in pediatric CM. Therefore, only single recurring SAEs within a MedDRA classification group will initiate a pause for safety review. The properties for the halting rules were estimated by Monte Carlo simulation with 100,000 replicates. At any halt, the DSMB will review the data and evaluate whether the study should stop due to safety concerns.

Although we will only report SAEs to the regulatory bodies that have a reasonable possibility of being related to the intervention, for the purpose of applying halting rules, all events (deaths, disability, etc.), even if not specifically reported as SAEs related to treatment, will be documented.

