### Primary endpoints

In adult participants, the primary endpoint is any grade 2 or 3 AE or SAE in the 14 days after DON administration. In pediatric participants with CM, the primary endpoint includes any SAEs at any time within 14 days after DON administration. The list of solicited AEs is based on known AEs from previous DON trials. All other AEs are documented as unsolicited events. AE grading (Tables 2 and 3) was adapted from the National Institute of Allergy and Immunology (NIAID) Division of AIDS (DAIDS) toxicity tables criteria [43].

**Table 2 Tab2:** Toxicity grading scales for adult participants

Parameter	Grade 1	Grade 2	Grade 3
White blood cells (10^3^/μL)	2.0 to 2.39 if normal baseline 35% reduction from baseline, if abnormal baseline	1.5 to 1.99 if normal baseline 50% reduction from baseline, if abnormal baseline	Less than 1.5 if normal baseline 65% reduction from baseline, if abnormal baseline
Hemoglobin (g/dL)			
Healthy male Normal baseline	10 to 10.9	9 to < 10	< 9
Healthy female Normal baseline	9.5 to 10.4	8.5 to < 9.5	< 8.5
Uncomplicated malaria^a^	35% reduction from baseline	50% reduction from baseline	65% reduction from baseline
Platelets (10^3^/μL)	100 to 116 if normal baseline 35% reduction from baseline, if abnormal baseline	50 to 99 if normal baseline 50% reduction from baseline, if abnormal baseline	< 50 if normal baseline65% reduction from baseline, if abnormal baseline
Serum creatinine	1.1–1.3 × ULN	> 1.3 to 1.8 × ULN	> 1.8 × ULN
Serum SGOT	1.25 to < 2.5 × ULN if normal baseline	2.5 to < 5.0 × ULN if normal baseline	≥ 5.0 × ULN if normal baseline
	35% increase from baseline, if abnormal baseline	50% increase from baseline, if abnormal baseline	65% increase from baseline, if abnormal baseline
Diarrhea	3 or more loose stools in 24 h, treated with dietary changes	6 or more loose stools in 24 h requiring IV rehydration for clinical stabilization, resolving within 36 h	≥ 6 loose stools in 24 h requiring IV rehydration for clinical stabilization, not resolving within 36 h
Gastrointestinal bleeding	Coffee ground emesis or positive stool hemoccult or frank bleeding with < 10% decrease in hematocrit/PCV	Coffee ground emesis or positive stool hemoccult or frank bleeding with a ≥ 10% decrease in hematocrit/PCV not requiring transfusion	Coffee ground emesis or positive stool hemoccult or frank bleeding with a ≥ 10% decrease in hematocrit/ PCV requiring transfusion

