### Adverse event reporting and harms {22}

AEs are collected within 14 days after DON administration. All AEs, including solicited local injection site and systemic (subjective and quantitative) reactions, are captured on the appropriate data collection forms and eCRFs. AE information includes event description, date of onset, assessment of severity using a protocol-defined grading system (Tables 2 and 3), relationship to study product and alternate etiology as assessed by a licensed study clinician, date of resolution, seriousness, and outcome. AEs are managed by the study team and referrals for further care are made on a case-by-case basis. All AEs are clinically followed through resolution.

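### Read literally, the pediatric vomiting scale in Table 3 leaves more than 6 episodes without hypotension ungraded or only grade 2, and it does not match the adult scale in Table 2

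*Protocol article*

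**What the plan says.** Under Primary endpoints, the protocol article gives separate toxicity scales for adults (Table 2) and children (Table 3). The vomiting row for children reads:

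- Grade 1: "1–3 episodes in 24 h with no or mild dehydration"
- Grade 2: "4–6 episodes in 24 h or any amount of vomiting with moderate dehydration requiring intensive intravenous rehydration"
- Grade 3: "More than 6 episodes in 24 h resulting in persistent hypotension"

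The adult row has the same grade 1 and, apart from trivial wording, the same grade 2. Its grade 3 is "> 6 episodes in 24 h or any amount of vomiting resulting in persistent hypotension".

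The section on adverse event reporting (item 22) makes these tables the severity scale, since AE information includes "assessment of severity using a protocol-defined grading system (Tables 2 and 3"). On relevance, Background and rationale says of the earlier DON trials: "The most commonly reported adverse effects in these studies were nausea and vomiting". Table 3 has no nausea row, so in children vomiting alone represents this toxicity among the graded parameters.

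**The concern.** A severity scale should give every event a grade, and a worse event should not receive a lower one. The pediatric row fails on both counts because grade 3 needs a high episode count and hypotension together, while grade 2 stops at 6 episodes unless there is moderate dehydration.

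The words that supply the alternative in the adult grade 3 cell are absent from the pediatric cell, although the equivalent words are present in the pediatric grade 2 cell next to it. That looks more like a slip than a decision. Where Table 3 sets a parameter aside because of cerebral malaria (hematocrit, glucose, lactate), it says why; the vomiting row carries no such reason.

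At stake is the severity profile of vomiting in children. The DSMB reviews solicited and unsolicited AEs and makes recommendations on dose escalation (item 21a). The intervention description (item 11a) says that escalation above 1.0 mg/kg in children draws on safety and tolerability in the adult cohorts and in the first three pediatric cohorts. For vomiting, those two sources would be graded on different scales.

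**Working it through.** The document states no figure to reproduce; the check is one of logic.

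**Inputs.** The three pediatric cells of Table 3 and the adult grade 3 cell of Table 2. Let n be episodes in 24 h and n ≥ 1.

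- Grade 1, both tables: n = 1–3 and no or mild dehydration.
- Grade 2, both tables: n = 4–6, or any n with moderate dehydration needing intensive IV rehydration.
- Grade 3, Table 3: n > 6 **and** persistent hypotension.
- Grade 3, Table 2: n > 6 **or** persistent hypotension.

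The highest grade met is assigned.

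**Grid.** n = 2, 5, 7 or 10; dehydration none, mild or moderate; hypotension yes or no. That is 4 × 3 × 2 = 24 combinations. The rows disagree in these:

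| Episodes | Dehydration | Hypotension | Table 3 (children) | Table 2 (adults) | Combinations |
|---|---|---|---|---|---|
| 7 or 10 | none or mild | no | no grade | 3 | 4 |
| 7 or 10 | moderate | no | 2 | 3 | 2 |
| 2 | none or mild | yes | 1 | 3 | 2 |
| 2 | moderate | yes | 2 | 3 | 1 |
| 5 | any | yes | 2 | 3 | 3 |

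The total is 4 + 2 + 2 + 1 + 3 = 12 of 24, and the pediatric grade is lower or absent in each. The other 12 agree. The count describes the rules; the cells are not equally likely, so it is not a frequency.

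**Non-monotonicity within Table 3 alone.** With no dehydration and no hypotension, 2 episodes is grade 1, 5 is grade 2, and 7 or 10 has no grade. This needs no comparison with Table 2.

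**How often?** The document gives no distribution of episode counts. Suppose, purely as an assumption, that the count on the worst day is Poisson with mean m. Among children who vomit, the share with more than 6 episodes is

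P(X > 6 | X > 0) = [1 − Σ(k = 0 to 6) e^(−m) m^k / k!] / (1 − e^(−m))

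- m = 2: 0.0045 / 0.8647 = about 0.5%
- m = 3: 0.0335 / 0.9502 = about 3.5%
- m = 4: 0.1107 / 0.9817 = about 11%
- m = 5: 0.2378 / 0.9933 = about 24%
- m = 6: 0.3937 / 0.9975 = about 39%

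These are upper limits for the gap above 6 episodes, because children in that group who also have hypotension are graded 3. A range from 0.5% to 39% shows that the frequency is unknown. Nothing in the document supports one mean over another, and ondansetron cover and the holding of feeds for 24 h mean that low values cannot be left out.

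**The case against.** The strongest reply is that little of consequence depends on the grade.

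- **Primary endpoint and halting.** A reader might infer that misgrading distorts the pediatric primary endpoint or the stopping rule. It does not. The endpoint is stated as "In pediatric participants with CM, the primary endpoint includes any SAEs at any time within 14 days after DON administration", and the halting rule as "The pediatric study pauses enrollment if the number of participants with SAEs in any single MedDRA group exceeds rates expected in children with CM". Grade 2 or 3 AEs enter the primary endpoint in adults only. The article does expand SAE as severe in the Figure 1 legend and the adult halting criteria, but its abbreviation list says serious, and item 22 records severity and seriousness as separate items. A route from vomiting grade to the primary endpoint is therefore not supported.
- **Dose choice.** A reader might infer that vomiting grade is a formal input to the cohort 4 dose. The interim analysis section names the primary safety endpoint and the exploratory efficacy endpoints. Any influence of grade is indirect, through the general safety and tolerability review.
- **Lost events.** All AEs are captured with description, seriousness, relationship and outcome, and the DSMB sees them unblinded. Only the severity label is missing or lower.
- **Bias between arms.** The pediatric part is randomized and blinded, with one scale for both arms. Absolute grade 3 counts would fall; the main effect on the DON–placebo comparison is lost sensitivity.
- **Comparability.** No planned analysis compares adult and pediatric grades, and the tables already differ on creatinine, nausea and other rows.
- **Intent.** A stricter grade 3 in critically ill children could be deliberate, and the document does not show which cell, if either, is the slip.

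All of this stands and limits the size of the point. None of it closes the gap: even a deliberately stricter grade 3 would not explain why more than 6 episodes can be ungraded when 4–6 is grade 2. Reading the adult cell as requiring hypotension in both limbs does not help either. It would make the episode count redundant there, and the hole in Table 3 would remain.

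**Conclusion.** The point holds as a minor defect of wording. As written, the pediatric vomiting scale is incomplete and not monotone, and it differs without explanation from the adult scale at grade 3. The effect is confined to the severity grading of pediatric vomiting AEs, and so to one part of the safety and tolerability picture that the DSMB sees when it considers escalation.

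The conclusion rests on a literal reading of Table 3, whose vomiting row appears intact in the text at hand. The frequency cannot be derived from the document. Whether the full protocol or the CRF grading guide has the same wording, and whether any event has been misgraded, is not known from the article. The document also does not establish that the adult wording is the correct one.

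**What to change.** Reconcile the vomiting rows of Tables 2 and 3 so that every episode count in children has a grade and the grade never falls as the event worsens. Restoring the Table 2 alternative in the pediatric grade 3 cell is one way. If the stricter condition is intended, state and justify it, and still assign a grade to more than 6 episodes without hypotension. Which criterion to adopt is for the sponsor to decide.

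Check the full protocol and the CRF grading guide for the same wording. If it is there, re-derive any pediatric vomiting grades already assigned under it; this can be done without unblinding the study team if episode counts, dehydration and hypotension were recorded.

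The cost is one table cell, the matching entry in the grading guide, and a short re-derivation. The downside is that a few events may be graded higher than before. The pediatric primary endpoint, halting rule and sample size are unaffected.
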